As a TA model, the Coalition Check-Up requires 84% less TA time compared to the TA used in Communities That Care and PROSPER (4% FTE per coalition vs. 25% FTE). The Coalition Check-Up TA model is a low-intensity yet tailored solution to the tension between TA effectiveness and cost constraints. It is not specific to a particular community coalition model (e.g., PROSPER) or EBP, instead focusing on common dimensions of coalition capacity and program implementation intended to improve youth outcomes [20, 21]. Such a “light touch” intervention would be more easily sustained and is more likely to be adopted to support sustainability on a national scale than existing evidence-based TA models. Additionally, we do not yet know how coalitions can sustain implementation once TA diminishes. Although coalitions may continue to operate, their engagement and activities tend to decline when TA funding ends [22]. After TA loss, some coalitions have seen large declines in recruitment rates and implementation quality for prevention programming [22, 23]. One potential benefit of the Coalition Check-Up is preventing the usual loss of functioning among coalitions as they lose funding for TA. If effective, the Coalition Check-Up will provide lower-cost and thus more sustainable TA to help community coalitions implement EBPs.

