### Coalition recruitment

We will recruit 68 coalitions from community anti-drug coalitions across Pennsylvania and Missouri, USA. This coalition population is similar to other US coalitions, which enhances study generalizability. These coalitions have received funding from a wide variety of sources, and their activity levels have fluctuated with changes in funding levels over time. Coalitions function in rural, suburban, and urban areas, ranging in age from 1 to 30 years old. We connect with these coalitions through the Evidence-based Prevention and Intervention Support (EPIS) group in the Pennsylvania State University’s Prevention Research Center. The EPIS team interfaces with community agencies, schools, and coalitions to provide support to those attempting to integrate prevention research into their practices.

We are using a layered targeted strategy to recruit coalitions, first with email communications from EPIS TA staff. We then introduce the project at coalition regional meetings organized by EPIS, providing time for questions and small group discussion to connect project researchers with coalition members. We then conduct follow-up phone calls and online meetings. The decision to participate rests on each coalition’s leadership team or at times with the full coalition.

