### Randomization

Matched pairs of coalitions will be randomly assigned to the Coalition Check-Up condition or TA as usual. Coalitions will be matched on level of TA availability at baseline (0 = none, 1 = occasional trainings and group TA, 2 = regularly scheduled group TA, 3 = group TA and regularly scheduled one-on-one supervision, 4 = regularly scheduled one-on-one capacity-building TA), years in operation, coalition model employed, population density, US Census poverty rate, and availability of funding. A random number seed will be generated by an external third party using random.org. SAS Proc Surveyselect uses this random number seed to select one of each pair of coalitions recruited into the study as the intervention condition. Data collectors and data analysts will be blind to study condition, with no circumstances under which unblinding is permissible.

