### Power analysis

We used Optimal Design to estimate power for cluster-randomized trials [60]. In this study, youth-level substance use data and program-level implementation data are clustered within coalitions, which is the level of random assignment. Overall, we will have a power of .80 to detect Cohen’s *d* effect size ranges as follows: aim 1, .24 to .37, a small to medium effect, depending on the measure of coalition capacity; aim 2, .31 to .42, a medium effect, depending on the EBP implementation measure; and aim 3, .25, a small effect, for measures of youth substance use.

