### Data analytic plan

For aim 1, multi-level longitudinal growth models will be used to test our hypotheses that coalitions assigned to the Coalition Check-Up condition will show improving coalition capacity over time compared to the comparison condition. Our first step entails testing for baseline differences on all measures of coalition capacity between the two experimental conditions. All models will be estimated in MPlus using full information maximum likehood, which has the advantage of being able to estimate missing data [61].

We will model coalition structural characteristics (decentralization, multiplexity, sectoral diversity, intersectoral communication) as coalition-level dependent variables for aim 1. These dependent variables will be predicted by the experimental condition (0=control; 1= Coalition Check-Up), controlling for potential confounders (e.g., coalition model). Once we have multiple waves of data, measurement occasion will be repeated within coalition, and we will utilize growth modeling in our tests of Coalition Check-Up impact on coalition capacity. We will include pretest (i.e., year 0) measures in the model, enabling us to examine change in these characteristics over time between the two groups. Analyses will start by testing unconditional longitudinal models with maximum likelihood estimation in order to find the best functional form, after which we will test our hypotheses [62]. We will identify the trajectory of coalition capacity using model fit indices—including the AIC, BIC, and the −2 Log Likelihood deviance across different types of longitudinal models, including (a) the empty model (i.e., model with only a random intercept), (b) polynomial growth models, (c) polynomial growth models with random slopes, and (d) piecewise models [13, 62]. Once the developmental trajectory of coalition capacity is properly modeled, it will be predicted by experimental condition (0=control; 1= Coalition Check-Up), controlling for potential confounders.

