#### Aim 2: Plan of analysis

Using Mplus, we will test the three hypotheses that coalitions receiving the Coalition Check-Up will implement EBPs with greater (1) quantity, (2) quality, and (3) sustainability as compared to the “TA as usual” condition. Prior to hypothesis tests, we will test for baseline differences on each of these dependent variables.

To test aim 2’s first hypothesis, we will model EBP quantity as a coalition-level dependent variable. Once we have three time points of data, we will estimate the developmental trajectory of EBP quantity with growth models—following aim 1 procedures to identify the best functional form of the growth model. Once the developmental trajectory of EBP quantity is properly modeled, it will be predicted by the experimental condition (0=control; 1= Coalition Check-Up) [62].

For the second hypothesis—i.e., programs implemented by coalitions in the Coalition Check-Up condition have superior implementation quality—the unit of analysis is program level, nested within coalition level. Thus, the analytic model will estimate a random intercept. As in the first hypothesis, growth modeling procedures will estimate the developmental trajectory of EBP quality. Experimental condition (0=control; 1= Coalition Check-Up) will be entered at the level of the coalition. Program type (i.e., school-based curriculum, therapist-driven, mentoring, parent curriculum) and program complexity will be covariates at the program level.

For the third hypothesis—i.e., programs implemented by Coalition Check-Up coalitions have superior sustainability—we will test overall EBP sustainability and sustainability planning separately. Coalition Check-Up impact on sustainability planning will be estimated with a multilevel model accounting for the nesting of programs within coalitions. Program-level covariates include program type, program complexity, and baseline EBP longevity. Since overall EBP sustainability is a coalition-level dependent variable, the regression model will not need to adjust for the nesting of programs within coalitions. As with prior models, experimental condition (0=Control; 1= Coalition Check-Up) will be entered at the coalition level.

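### The growth form is chosen before condition enters and may be intercept-only, so the Aim 1 test of change over time can become a test of average level

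*Protocol article*

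**What the plan says.** The Aim 1 hypothesis in the protocol article's Data analytic plan concerns change: capacity should improve over time in Check-Up coalitions relative to comparison coalitions. The modelling sequence has three steps.

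- Form first: "Analyses will start by testing unconditional longitudinal models with maximum likelihood estimation in order to find the best functional form".
- The candidates are compared by AIC, BIC and −2 log likelihood. They start with "a) the empty model (i.e., model with only a random intercept", followed by polynomial growth models, polynomial models with random slopes, and piecewise models.
- Condition last: "Once the developmental trajectory of coalition capacity is properly modeled, it will be predicted by experimental condition".

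The paragraph on member-level cohesion and efficiency says that model fit will be tested by the same process. For EBP quantity, Aim 2 proceeds by "following aim 1 procedures to identify the best functional form of the growth model". EBP quality refers back to growth modelling in more general terms.

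The section also says that the year-0 measure is in the model so that change can be compared between groups. It does not say whether year 0 is the first repeated outcome or a covariate. It does not say which index decides when AIC and BIC disagree, or that a condition-by-time term stays in the model whatever form is selected.

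**The concern.** An unconditional model leaves condition out, so with equal arms its mean slope is the average of the two arm slopes. If one arm rises about as fast as the other falls, the pooled line is flat and the fit indices favour the intercept-only model. Nothing in that model describes time, so condition can predict only the coalition's mean level over the waves. For a gap that opens linearly from zero, that mean difference is half the final gap if year 0 is among the waves, and it does not measure change.

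The step meant to describe time can therefore remove the contrast that the Aim 1 hypothesis names, and it can do so for some outcomes and not others, depending on the data. Some divergence in direction is plausible on the protocol's own account. It expects improvement under Check-Up, and its Background says "One potential benefit of the Coalition Check-Up is preventing the usual loss of functioning among coalitions as they lose funding for TA".

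**Working it through.** **The plan's own figure.** The Power analysis says "Overall, we will have a power of .80 to detect" d of .24 to .37 for Aim 1. With 34 coalitions per arm, two-sided alpha .05 (assumed) and no covariate, the detectable d for a coalition-level measure is (1.960 + 0.842) × √(2/34) = 0.68. Reaching .37 or .24 needs R² of 1 − (.37/.68)² ≈ .70 or 1 − (.24/.68)² ≈ .88. Member-level measures can reach the range: 10–25 members per coalition and ICC .02–.20 give .165–.36. No ICC, cluster size or R² is stated, so the range can be neither confirmed nor refuted. It is not used below.

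**Inputs from the protocol.** "We will recruit 68 coalitions from community anti-drug coalitions across Pennsylvania and Missouri, USA", with SAS used to "select one of each pair of coalitions recruited into the study as the intervention condition", gives 34 per arm. Annual collection for 4 years gives waves 0, 1, 2, 3.

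**Assumptions.** Unit total variance; wave-to-wave ICC ρ of .3, .5 or .7; a linear gap from 0 at year 0 to d at wave 3; alpha .05 two-sided.

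**Closed form.** In each case the effect is divided by SD × √(2/34). The sum of squared centred times is 5.

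- Condition-by-time: effect d/3, SD √((1−ρ)/5).
- Intercept-only, year 0 a repeated outcome: effect d/2, SD √(ρ + (1−ρ)/4).
- Intercept-only, year 0 a covariate: effect 2d/3, SD √(ρ + (1−ρ)/3 − ρ²).

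For each ρ, d is set so that the condition-by-time test has power .80. At ρ = .5, d = 3 × 2.802 × 0.316 × 0.2425 = 0.645. The intercept-only test then has z = 0.322 / (0.791 × 0.2425) = 1.68 and power .39.

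| ρ | d at wave 3 | Condition-by-time | Intercept-only, year 0 repeated | Intercept-only, year 0 covariate |
|---|---|---|---|---|
| .3 | .763 | .80 | .63 (22% lost) | .88 (none lost) |
| .5 | .645 | .80 | .39 (51% lost) | .78 (2% lost) |
| .7 | .499 | .80 | .215 (73% lost) | .69 (13% lost) |

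This shows the cost once the intercept-only model has been chosen.

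**How often it is chosen.** Simulation, 400 runs per setting (Monte Carlo standard error at most .025), year 0 a repeated outcome. Unconditional candidates were intercept-only, linear, quadratic and linear with random slope, fitted by ML; the piecewise candidate was left out. Condition was then tested in the selected form. Each cell gives ρ = .5 with d = .66 / ρ = .7 with d = .50.

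| Setting | Intercept-only chosen, BIC | Intercept-only chosen, AIC | Power, BIC | Power, AIC | Power, condition-by-time always kept |
|---|---|---|---|---|---|
| Equal and opposite, no other slope variation | 98% / 98% | 69% / 77% | .44 / .22 | .56 / .34 | .82 / .80 |
| One quarter improvement, three quarters decline | 86% / 84% | 42% / 44% | .49 / .34 | .64 / .55 | .80 / .78 |
| Check-Up flat, controls decline | 31% / 33% | 7% / 4% | .68 / .59 | .78 / .77 | .82 / .80 |
| Equal and opposite, slope SD 0.1 per year | 97% / 97% | 64% / 57% | .42 / .26 | .54 / .44 | .78 / .74 |
| Equal and opposite, slope SD 0.2 per year | 82% / 67% | 20% / 13% | .41 / .32 | .62 / .52 | .65 / .58 |

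The last column uses the random-slope model where slopes vary.

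**Why the random-slope candidate helps only sometimes.** At d = .66 the arms differ by .22 per year, so each lies .11 from the pooled slope. Condition alone then contributes slope variance .11² = .012, against a within-coalition sampling variance of .5/5 = .10. That is too small to be picked up reliably: AIC chose random slopes in 13% / 8% of runs when there was no other slope variation, and in 74% / 84% at slope SD 0.2.

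**The case against.** The strongest reply is that nobody would end with an intercept-only model here. The hypothesis is about change, the pretest is included so that change can be compared, and the intercept-only model is the customary baseline comparator. That is probably the intent. But the text lists it as a candidate for the trajectory that condition will predict, and no sentence rules it out.

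Three further points limit the size of the problem, and they stand.

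- The protocol does not describe equal and opposite trends. The Background speaks of preventing decline, and ties decline to the end of TA funding, while the Method section gives both arms continued access to TA as usual. If Check-Up merely holds steady, the pooled slope is usually kept.
- A reader might infer that no slope can survive. That overlooks the random-slope candidate, which under AIC limits the loss to about 5–10% at slope SD 0.2. It does much less at SD 0.1 (31–41% lost) or under BIC.
- If year 0 is a covariate, even the intercept-only model loses little.

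For Aim 2 quantity, the hypothesis is greater quantity, so a level difference is not off-target there. What remains is that the quantity estimated depends on the data. An analysis plan that is not shown may settle some of this, but the sequence in the article is stated and would need correcting.

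**Conclusion.** The sequence as written can replace the Aim 1 change-over-time test with a diluted average-level test, because condition-by-time is not protected from a selection step that cannot see condition. That follows from the text alone.

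The size is conditional. Under near-equal opposite linear trends, no other slope variation, year 0 as a repeated outcome and ICC .5–.7, power falls from about .80 to .22–.44 under BIC and .34–.56 under AIC. With Check-Up flat and controls declining, the loss is about 4–5% under AIC and 17–26% under BIC. With year 0 as a covariate it is at most about 13%.

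A reader might infer that the plan forfeits about half its power. The documents do not support that as a general figure: across the settings computed the loss runs from about 0 to 73%, and the protocol states no ICC, slope variance, arm-specific trend or deciding index. The member-level models were not simulated.

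**What to change.** State that the condition-by-time term is retained in every Aim 1 growth model, and in the Aim 2 quantity model that reuses the procedure, whatever the unconditional fit shows. Keep the intercept-only model as a baseline comparator only. If fit indices are still to choose the time shape, apply them to models that already contain condition and condition-by-time. It would help to say in the same place whether year 0 is a repeated outcome or a covariate, and which index decides. Treating wave as a category, or naming a single contrast, would also work but is a matter of preference.

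The cost is wording, plus one or two extra mean parameters per model. Design and data collection are unaffected.

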#### Aim 2: Plan of analysis

Using Mplus, we will test the three hypotheses that coalitions receiving the Coalition Check-Up will implement EBPs with greater (1) quantity, (2) quality, and (3) sustainability as compared to the “TA as usual” condition. Prior to hypothesis tests, we will test for baseline differences on each of these dependent variables.

To test aim 2’s first hypothesis, we will model EBP quantity as a coalition-level dependent variable. Once we have three time points of data, we will estimate the developmental trajectory of EBP quantity with growth models—following aim 1 procedures to identify the best functional form of the growth model. Once the developmental trajectory of EBP quantity is properly modeled, it will be predicted by the experimental condition (0=control; 1= Coalition Check-Up) [62].

For the second hypothesis—i.e., programs implemented by coalitions in the Coalition Check-Up condition have superior implementation quality—the unit of analysis is program level, nested within coalition level. Thus, the analytic model will estimate a random intercept. As in the first hypothesis, growth modeling procedures will estimate the developmental trajectory of EBP quality. Experimental condition (0=control; 1= Coalition Check-Up) will be entered at the level of the coalition. Program type (i.e., school-based curriculum, therapist-driven, mentoring, parent curriculum) and program complexity will be covariates at the program level.

For the third hypothesis—i.e., programs implemented by Coalition Check-Up coalitions have superior sustainability—we will test overall EBP sustainability and sustainability planning separately. Coalition Check-Up impact on sustainability planning will be estimated with a multilevel model accounting for the nesting of programs within coalitions. Program-level covariates include program type, program complexity, and baseline EBP longevity. Since overall EBP sustainability is a coalition-level dependent variable, the regression model will not need to adjust for the nesting of programs within coalitions. As with prior models, experimental condition (0=Control; 1= Coalition Check-Up) will be entered at the coalition level.

Mediation analyses will test whether coalition capacity mediates between intervention condition and EBP implementation. We will test whether coalition capacity has significant direct and indirect effects on each EBP implementation measure: (a) quantity, (b) quality, and (c) sustainability. Each of these outcomes will be modeled as previously described in this aim, with the addition of the coalition capacity mediational pathway [63, 64].

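### The two Aim 2 sustainability models name no baseline measure of the outcome; for the coalition-level total, the detectable effect is then about d = 0.69

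*Protocol article*

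**What the plan says.** Under the Aim 2 plan of analysis, baseline comparisons come first: "Prior to hypothesis tests, we will test for baseline differences on each of these dependent variables". No use of the result is stated. The outcomes are then handled in two ways.

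- **EBP quantity and quality** get growth models. Quantity follows the Aim 1 procedures, which put the year-0 measure in the model, and quality uses the same growth approach.
- **Sustainability** gets two separate models, neither described as a growth model. For planning: "Program-level covariates include program type, program complexity, and baseline EBP longevity". For the overall measure: "Since overall EBP sustainability is a coalition-level dependent variable, the regression model will not need to adjust for the nesting of programs within coalitions". The text adds only that condition enters at coalition level and names no covariate.

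The Aim 2 measures section says the EBP facets are assessed every year. It defines overall sustainability as a coalition-level total of program-years over years 2–4, counting programs already running as well as new ones. Planning is a program-level score. The Randomization section matches coalitions on TA availability, years in operation, coalition model, population density, poverty rate and funding. The number of EBPs is not on that list.

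The Power analysis section gives power of .80 for d = 0.31 to 0.42 in Aim 2, varying by measure. It does not say which figure belongs to which measure, and gives no alpha, ICC, programs per coalition or R².

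**The concern.** A coalition that enters with more programs will tend to accumulate more program-years in years 2–4 whatever the technical assistance does. If the model ignores that starting point, the between-coalition spread stays in the error term, and a chance difference in starting programs moves the estimate. With only 68 randomised units this matters for precision. The same logic applies, less sharply, to the planning score, where baseline EBP longevity is a partial stand-in.

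The plan also tests for baseline differences without saying what follows from a significant result. In Aim 2 this leaves open whether covariates will be chosen after the baseline data are seen. Aim 3 does state such a rule: a measure that differs at baseline becomes a covariate.

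**Working it through.** **Inputs from the article.** "We will recruit 68 coalitions from community anti-drug coalitions across Pennsylvania and Missouri, USA" (Coalition recruitment). The allocation procedure is to "select one of each pair of coalitions recruited into the study as the intervention condition" (Randomization), hence 34 v 34. Power is .80, and the Aim 2 range is 0.31–0.42 (Power analysis).

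**Assumed, because not stated.** Two-sided alpha of 0.05; ICC 0.01–0.30; 1–10 programs per coalition; baseline–outcome correlation r from 0 to 0.9.

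**The plan's own figure.** The range 0.31–0.42 cannot be reproduced, since alpha, ICC, programs per coalition and R² are not given.

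**Overall EBP sustainability (one value per coalition), no covariate.** Detectable d = (t.975 + t.80) × √(4/68), with 66 df.
- t version: 2.844 × 0.2425 = 0.69.
- Normal approximation: (1.960 + 0.842) × 0.2425 = 0.68.
- Paired df (33): 0.70. One-sided: 0.61.

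Every variant lies above 0.42. Two-sided power is about 41% at d = 0.42 and 25% at d = 0.31. An unadjusted test would need 89 coalitions per arm for 0.42 and 164 for 0.31.

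**R² needed to reach the stated range.**
- For 0.42: 1 − (0.42/0.69)² ≈ 0.63, so r ≈ 0.79.
- For 0.31: 1 − (0.31/0.69)² ≈ 0.80, so r ≈ 0.89.

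**With one baseline covariate,** d ≈ 0.69 × √(1 − r²):

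| r | Detectable d | Power at 0.42 |
|---|---|---|
| 0.3 | 0.66 | 44% |
| 0.5 | 0.60 | 52% |
| 0.7 | 0.49 | 68% |
| 0.8 | 0.41 | 82% |
| 0.9 | 0.30 | 98% |

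The article gives no value for r.

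**Sustainability planning (program level), no covariate.** Detectable d = 0.69 × √[ICC + (1 − ICC)/m], with m programs per coalition.
- ICC 0.05, m = 3: √0.367 = 0.606, so d = 0.42.
- ICC 0.10, m = 4: √0.325 = 0.570, so d = 0.39.
- ICC 0.05, m = 6: √0.208 = 0.456, so d = 0.31.
- m = 2, ICC 0.05 to 0.30: d = 0.50 to 0.56.

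The stated range is therefore attainable here without the baseline score in some cases and not in others. The possible gain from adjustment at ICC 0.10 and m = 3 is from 0.44 to 0.38 (R² 0.25), 0.35 (R² 0.36) or 0.31 (R² 0.50), taking R² as equal at both levels.

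**Baseline tests.** Three Aim 2 outcomes have a literal baseline value: quantity, quality and planning. If the tests were independent, at least one would be significant by chance with probability 1 − 0.95³ = 14.3%. The tests are probably correlated, so this is only a guide.

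**The case against.** The strongest reply is that this is a condensed article. The sentence on overall sustainability is about nesting and is not a closed covariate list, and the planning list says only that covariates include three items. Fuller lists may sit in the SAP. That is fair, and it is why the point is limited to what the article names. The contrast within the article remains: pretest measures are written into Aim 1 and carried into the quantity and quality growth models, but not into the sustainability pair.

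Other replies also have weight:
- Chance imbalance is not bias; the standard error already reflects it. This is a question of precision.
- Overall sustainability has no baseline value, so any covariate is an analogue that someone must choose.
- Matching on years in operation, funding and TA availability may limit imbalance in starting programs. Variance explained by the pairs would count towards R² if the analysis used them, but the article does not say that it does.
- In Aims 1 and 2 no stated action depends on the baseline tests.

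A reader might infer that the stated detectable effects are out of reach for both sustainability models, and that the missing baseline terms are the cause. The article does not support that. Planning is a program-level outcome to which 0.69 does not apply. The range 0.31–0.42 is not tied to particular measures. Adjustment brings the coalition-level figure to 0.42 only if r is about 0.79 or more.

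**Conclusion.** The point holds as one of efficiency and specification. As written, neither sustainability model names a baseline measure of its outcome, although the relevant baseline information should be available from the annual assessments.

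For overall EBP sustainability the unadjusted detectable d is about 0.69 (0.61–0.70 across the variants tried), well above the top of the Aim 2 range. No choice of ICC or programs per coalition changes that, because each coalition supplies one value. Only explained variance can, and the named model includes no variable to supply it. A baseline EBP count would help by an amount that depends on an unknown correlation, and it may still fall short of 0.42.

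For sustainability planning the gain may be worthwhile, but no shortfall against the stated range is shown.

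It would also go too far to say that year-0 values are missing throughout Aims 1 and 2, since the growth models already use them. Dropping the baseline significance tests altogether is a minor matter. What counts is that they do not select covariates.

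**What to change.** 1. **Overall EBP sustainability:** pre-specify the number of EBPs operating at baseline as a covariate, entered as zero where there is none.
2. **Sustainability planning:** add the baseline planning score to the listed covariates. Give new programs their coalition's baseline mean. Use a missing-baseline indicator for coalitions with no EBP at baseline; these can occur because eligibility admits coalitions that have only secured funding. Define that indicator at coalition level, since whether a program is new is settled after randomisation.
3. **Baseline tests:** state that both covariates stay in whatever these tests show, and that the Aim 2 tests are not used to choose covariates.
4. **Power analysis:** restate the detectable effect for the coalition-level sustainability outcome with its assumed R², and give the alpha, ICC and programs per coalition behind 0.31–0.42.

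No change is needed where growth models already include year 0. The cost is wording, one or two degrees of freedom per model, and a rule for absent baselines. No new data collection should be needed.
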